### Interim analyses {21b}

No interim analyses are planned.

### Methods for additional analyses (e.g. subgroup analyses) {20b}

Subgroup analyses will be performed to examine for statistical interaction between the treatment arm and (1) initial response to 2-dose vaccine schedule (non-responder or low-responder) and (2) duration between previous vaccine dose (less than, or greater than 6 weeks) and randomisation. Patients who develop primary COVID-19 infection during the study period will have both primary and secondary outcomes analysed as a pre-specified subgroup analysis.

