## Introduction

### Background and rationale {6a}

Kidney transplant recipients (KTRs) are at an increased risk of COVID-19 associated morbidity and mortality, with the combined effects of immunosuppression and prevalent comorbidities contributing to the high rates of adverse outcomes [1, 2]. Meta-analyses have suggested a 28-day mortality approaching 25% for KTRs positive for SARS-CoV-2, and survivors have significant risk of morbidity including hospitalisation, acute kidney injury, and graft loss [2].

The development of effective vaccines which target the SARS-CoV-2 spike protein has been crucial to reducing disease burden and the development severe COVID-19 disease [3]. However, immunocompromised populations such as KTRs were excluded from initial vaccine trials. KTRs exhibit suboptimal vaccine responses and are inadequately protected by current standard two- and three-dose vaccine regimes [4, 5].

To address the inadequate vaccine response observed in KTRs and other immunocompromised groups, additional doses of mRNA vaccine have been recommended. In KTRs, data from a randomised controlled trial suggest that a third mRNA vaccine dose increases the proportion of patients with protective neutralising antibodies to 60%, compared to 25% in the placebo group [6]. While a third vaccine dose improves vaccine immunogenicity, to what extent seropositive patients are protected is unclear, and a significant minority of KTRs fail to seroconvert and therefore require additional strategies [6–8].

Observational data suggests that vaccine responses are significantly affected by immunosuppression regimen. The use of mycophenolate has been identified as a key factor associated with vaccine hypo-responsiveness [5]. Such observations are consistent with earlier reports identifying mycophenolate use as being strongly associated with infection risk among maintenance-phase KTRs, and that use of mycophenolate was associated with inadequate responses to influenza vaccination [9–12]. Conversely, mechanistic target of rapamycin inhibitors (mTORi) have been found to boost vaccine-elicited cytotoxic T cell memory responses in non-human primates, and to improve antibody responses to influenza vaccination in elderly individuals [13, 14]. A recent, multicentre study of over 2000 KTRs reported a 50% reduction in viral infections among KTRs randomised to an mTORi-based regimen, as compared to those receiving mycophenolate, calcineurin inhibitor, and steroid [15, 16].

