### Management of COVID-19-positive participants during the trial

Study participants who returned a positive COVID-19 result during the trial will be managed in consultation with their treating transplant unit as per local best practice. Participants who contract COVID-19 following randomisation but prior to a third vaccination may have their third vaccine dose delayed. Where possible, participants will be asked to continue with their allocated treatment regimens and attend study visits and follow-up. Positive COVID cases will be excluded from the primary analysis as SARS-CoV-2 infection will confound assessment of the primary outcome measure.

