#### Secondary outcome measures

The secondary outcome measures include the following:2.The proportion of participants in each trial that reach a threshold of serological anti-SARS-CoV-2 (ancestral strain) RBD IgG antibody ≥ 100 units/mL (measured with an Elecsys Anti-SARS-CoV-2 immunoassay [Roche], and equivalent to 100 BAU/mL). This RBD IgG threshold was chosen on the basis of pre-clinical and clinical studies and is consistent with the reported outcomes in published COVID-19 clinical vaccine trials [6].3.The development of COVID-19 following randomisation, determined by:Positive SARS-CoV-2 PCR test, or rapid antigen test in the setting of symptomatic diseaseDetection of SARS-CoV-2 anti-nucleocapsid antibodies at the time of primary outcome assessment.4.Change in the median magnitude of the SARS-CoV-2 spike-specific, antiviral T cell response prior to and at 4–6 weeks following vaccination, determined as the frequency of cells that secrete IFNγ in response to stimulation with spike-protein (ancestral strain)-derived peptides.5.Phenotypic and functional characterisation of T and B lymphocyte populations6.Tolerance of sirolimus as determined by drug cessation, drug adherence, and drug-related adverse events including proteinuria, anaemia, leukopenia, rash, mouth ulcers, and pneumonitis.7.Adverse events following immunisation (AEFI) including adverse events of special interest (AESI) will be assessed via phone consultation at 1 week, and again at 4–6 weeks post-vaccination during the final follow-up visit, and include:Changes in kidney allograft function, determined by serum creatinine, eGFR (CKD-EPI equation), and proteinuriaThe occurrence of biopsy proven acute allograft rejectionThe recurrence of primary kidney diseasePatient-reported quality of life as recorded by the EQ-5D questionnaire8.Changes in the community structure, relative abundance, and functional characteristics of the gut microbiome following 4 weeks of sirolimus intervention, determined by 16S-rRNA metagenomic sequencing of participant stool samples.

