### Participant timeline {13}

Participants are followed from the time of enrolment through until study close-out, 1 week following their final assessment visit. The schedule of enrolment, randomisation, interventions, and assessments is shown in Fig. 2.

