### If blinded, circumstances under which unblinding is permissible, and procedure for revealing a participant’s allocated intervention during the trial {17b}

The design is open label with only outcome assessors being blinded so unblinding will not occur.

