## Statistical methods

### Statistical methods for primary and secondary outcomes {20a}

The primary analysis will be by intention-to-treat, with participants assessed according to their treatment allocation. Participants who develop a positive SARS-CoV-2 PCR result during the study will be excluded from the primary analysis to avoid confounding. A per-protocol analysis will also be reported, with participants who failed to adhere or tolerate sirolimus, and participants who withdrew or were lost to follow-up excluded from the analysis. A sensitivity analyses adjusting for potential confounding may be performed should significant imbalances in baseline characteristics between the treatment groups occur.

The primary endpoint is the proportion of patients who achieved a post-intervention serological neutralisation of live SARS-CoV-2 virus (20.2% of the mean neutralisation level of a standardised cohort of COVID-19 convalescent individuals) in both groups using the chi-square test. An unadjusted and adjusted relative risk (RR) will be calculated. For the adjusted RR estimate, the primary outcome of a threshold SARS-CoV-2 serological neutralisation titre will be analysed using a log-binomial regression model. The initial immune response to a two-dose vaccine schedule (anti-RBD IgG titre; low responder: 0.4–99 U/mL; or non-responder: <0.4 U/mL) will be included in the model as a fixed effect, with study site as a random effect.

Secondary outcomes will be analysed using univariate and multivariate methods dependant on the outcome type. Baseline characteristics and demographic data will be reported as mean ± SD for normally distributed data and median ± IQR for non-normally distributed data, with categorical variables reported as frequencies. All statistical analyses will be described in detail with arising publications. A two-sided significance level of 5% will be used for all analyses.

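### Participants infected after randomisation form a pre-specified subgroup: their results can only be descriptive, and the primary-analysis exclusion should stop at the outcome sample

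*Protocol article*

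**What the plan says.** All references are to the protocol article.

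- **Additional analyses {20b}.** The section opens: "Subgroup analyses will be performed to examine for statistical interaction between the treatment arm and (1) initial response to 2-dose vaccine schedule". Its second factor is the interval from the previous vaccine dose to randomisation. A separate sentence then adds the infected group: "Patients who develop primary COVID-19 infection during the study period will have both primary and secondary outcomes analysed as a pre-specified subgroup analysis".
- **Secondary outcome measures, item 3.** "The development of COVID-19 following randomisation" is a trial outcome, identified by PCR, by rapid antigen test with symptoms, or by anti-nucleocapsid antibody at the primary outcome assessment.
- **Eligibility criteria {10}.** Documented earlier infection, or detectable nucleocapsid IgG, excludes a patient from entry.
- **Management of COVID-19-positive participants.** "Positive COVID cases will be excluded from the primary analysis as SARS-CoV-2 infection will confound assessment of the primary outcome measure". Dose 3 may also be delayed in those infected before it.
- **Statistical methods {20a}.** "Participants who develop a positive SARS-CoV-2 PCR result during the study will be excluded from the primary analysis to avoid confounding". The same section sets a two-sided 5% level for every analysis.
- **Participant timeline {13}.** Follow-up runs to "study close-out, 1 week following their final assessment visit".

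**The concern.** The infected group sits beside two subgroups that are examined for interaction with treatment arm, but it is a different kind of group. Earlier infection is barred at entry, so membership depends wholly on what happens after randomisation. The article gives two reasons to expect treatment to affect it. The background cites a trial that "reported a 50% reduction in viral infections among KTRs randomised to an mTORi-based regimen", and the primary threshold was chosen because it corresponds to 50% protection from infection. If sirolimus works as hypothesised, the infected in one arm are a different selection of patients from the infected in the other.

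The group is also mixed. It pools infections before dose 3, between dose 3 and the sample, and possibly after the sample. The neutralisation result of someone infected before sampling reflects infection as well as vaccine, which is the article's own reason for leaving these participants out of the primary analysis.

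The risk is one of interpretation. A difference due to selection or chance could be reported as a planned finding. Similar results in the two arms, because infection raised both, could be read as the switch not working in infected patients.

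A related problem affects the exclusion itself. If the study lasts until close-out, a participant infected in the week after the outcome sample leaves the primary analysis, although that infection cannot have altered a sample already taken.

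**Working it through.** The article gives no expected infection count and no figure for this analysis, so the main check is structural. The calculations show scale only. Every rate marked as assumed is an illustration, not a trial figure.

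**1. Is the group defined before or after randomisation?** Two-dose response is a stratification factor, and the dose-to-randomisation interval ends at randomisation. Infection during the study is neither. With earlier infection excluded at entry, it is purely a later event, and item 3 counts it as an outcome.

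**2. How many infected participants might there be?**
- From the article: 60 per arm and 10% drop-out, so 60 × 0.9 = 54 per arm; planned difference 25 points.
- Assumed: protective response p = 0.35 (control) and 0.60 (sirolimus); infection risk r = 0.20 if unprotected and r/2 if protected.
- Risk = p × r/2 + (1 − p) × r.
- Control: 0.35 × 0.10 + 0.65 × 0.20 = 0.165, and 54 × 0.165 = 8.9 infected.
- Sirolimus: 0.60 × 0.10 + 0.40 × 0.20 = 0.140, and 54 × 0.140 = 7.6 infected.

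**3. How precise would an arm comparison be?** Taking the largest variance (proportion 0.5):
- Half-width = 1.96 × √(0.25/8.9 + 0.25/7.6) = 0.48, or ±48 points.
- With r = 0.10 it is ±69 points; with r = 0.30 it is ±40 points.
- With 6, 12 or 18 infected per arm (10%, 20% or 30% of 60), power to detect 25 points is about 13–15%, 22–27% or 32–39%, for control proportions from 25% to 60%.

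**4. How far does selection move the difference?** Share protected by vaccine among the infected = (p × r/2) / risk.
- Control: 0.035/0.165 = 21%. Sirolimus: 0.060/0.140 = 43%.
- The difference falls from 25 to about 22 points, before any effect of infection on the titre.
- The control rate is not stated in the article. At 20% v 45%, a pair for which 54 per arm gives 80% power, the risks are 0.180 and 0.155, the shares are 0.020/0.180 = 11% and 0.045/0.155 = 29%, and the difference is about 18 points.

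A harsher case can be built. Assume that 40% reach the threshold among those infected under either arm, with no treatment effect in them, and 80% among those infected only under control. If treatment prevents 25% of infections, the control proportion is 0.75 × 40% + 0.25 × 80% = 50% against 40%, a spurious −10 points. If it prevents 50%, the result is 60% against 40%, or −20 points. If it prevents none, the bias is zero. The data cannot show which case applies.

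**5. How long is the period after the sample?** A 28-day lead-in, 28 to 42 days to sampling and 7 days to close-out make 63 to 77 days. The last week is 7/77 = 9% to 7/63 = 11% of that time. This is a share of days, not of expected exclusions.

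**The case against.** **No arm test is stated.** The interaction sentence names only the two baseline factors. The sentence on infected participants stands apart and could mean no more than separate reporting of people left out of the primary set. It would therefore go too far to infer that the plan commits to a significance test between arms in this group. The ambiguity remains: the primary outcome is a proportion compared between arms, the analysis is called a pre-specified subgroup analysis, and the 5% level covers all analyses. An article may leave the method to a fuller document, but the point concerns how this one classifies the analysis.

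**Infected participants are not lost to every randomised comparison.** A reader might infer that they are. The text excludes them only from the primary analysis. Item 3 necessarily includes them, and no exclusion is stated for anti-RBD IgG, T-cell, tolerance or safety outcomes.

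**The figures do not demonstrate large bias.** Correct. In the first illustration selection moves the difference by about 3 points, and by about 7 at the lower control rate, well inside an interval of nearly ±50. The 10- and 20-point biases come from strata chosen to show the mechanism. The first model is also crude: it applies dose-3 protection from randomisation, although dose 3 follows a four-week lead-in, and it borrows a 50% figure that the article gives for the ancestral strain in the general population.

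**The close-out reading is literal.** No section equates the study, or the study period, with follow-up to close-out. The stated reason for the exclusion and the timing of nucleocapsid testing both point to infection before sampling. That supports the proposed wording, but no section gives an earlier cut-off.

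**Conclusion.** The point holds in limited form. A comparison of arms among infected participants is not protected by randomisation, and naming it in advance does not change that. It could be read as a treatment effect only by assuming that treatment does not alter who is infected, or that those spared infection have the same prognosis as those still infected. Neither can be checked in the trial.

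What the calculations establish is imprecision: about ±48 points at assumed risks of 14% and 17%, and ±40 to ±69 over the range tried. These use the planned numbers. The article reports that recruitment closed before reaching 120, so at the same infection risks the real comparison would be weaker. The size of any selection bias is unknown.

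A reader might go further and conclude that the trial's main result is compromised by this analysis. It is not: this is an additional analysis and leaves the primary result unchanged. The cut-off for the primary exclusion does affect who is in the primary set, but only if the study is taken to run to close-out.

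**What to change.** 1. **Additional analyses {20b}.** Take infection out of the subgroup analyses of treatment effect. State that infected participants will be described by arm and by timing (before dose 3, between dose 3 and the outcome sample, after the sample), with no between-arm test and no causal reading.
2. **Management of COVID-19-positive participants and Statistical methods {20a}.** Limit the primary-analysis exclusion to infections on or before the outcome sample, in the same words in both sections. The nucleocapsid test at the outcome assessment already helps to identify these.
3. **Optional.** Add a supportive neutralisation analysis in all randomised participants, with a stated strategy for infection. Counting infection as failure is one choice among several, and it changes the question from vaccine response alone to response without infection. If it is added after outcome data have been seen, the report should say so.

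Items 1 and 2 cost a few sentences and need no new data. By the article's dates the last visit was in April 2022, so they would govern analysis and reporting rather than conduct. The downside is that the infected group gets no formal test, which it could not have supported.

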### Methods in analysis to handle protocol non-adherence and any statistical methods to handle missing data {20c}

A per-protocol analysis will also be reported, with participants who failed to adhere or tolerate sirolimus, and participants who withdrew or were lost to follow-up excluded from the analysis. Multiple imputation will be used to handle data missing at random from baseline characteristics. Data missing at random for the primary and secondary outcome will not be imputed, with these cases excluded from ITT analysis. If > 10% of the primary outcome data is determined to be missing not at random, a best-worst and worst-best case sensitivity analyses will be performed.

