## Assignment of interventions: allocation

### Sequence generation {16a}

Participants will be randomised 1:1 to either sirolimus (intervention) or mycophenolate (control). Randomisation will occur via computer-generated stratified block randomisation with randomly permuted block sizes of 2, 4, and 6. Stratification will occur by site and the response to a two dose COVID-19 vaccine schedule (low responder anti-RBD IgG 0.4 - 99 U/mL; or non-responder, anti-RBD IgG < 0.4 U/mL).

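### Outcomes labelled missing at random are dropped from a set still called ITT and compared by an unadjusted test, while the planned stratum-adjusted analysis, which would largely correct for this, is not made primary

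*Protocol article*

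**What the plan says.** All references are to the protocol article.

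- **Missing outcomes {20c}.** "Data missing at random for the primary and secondary outcome will not be imputed, with these cases excluded from ITT analysis".
- **Missing baseline data {20c}.** "Multiple imputation will be used to handle data missing at random from baseline characteristics".
- **Sensitivity analysis for missing outcomes {20c}.** Short of its final verb, the rule reads: "If > 10% of the primary outcome data is determined to be missing not at random, a best-worst and worst-best case sensitivity analyses will be". Nothing is planned for outcomes judged missing at random.
- **Analysis set {20a}.** "The primary analysis will be by intention-to-treat, with participants assessed according to their treatment allocation".
- **Primary comparison {20a}.** The endpoint is compared "in both groups using the chi-square test". In addition, "An unadjusted and adjusted relative risk (RR) will be calculated". The adjusted RR comes from a log-binomial model in which the two-dose response category "will be included in the model as a fixed effect, with study site as a random effect".
- **Randomisation {16a}.** "Stratification will occur by site and the response to a two dose COVID-19 vaccine schedule". Both model covariates are therefore known for everyone randomised.

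**The concern.** Missing at random means that, given the observed variables, loss does not depend on the unseen outcome. Loss may still depend on arm, response stratum or site. Deleting the lost cases and comparing crude proportions needs more than that: within each arm, loss must be unrelated to outcome. The two-dose response stratum was chosen as a stratification factor, presumably because it predicts response to the third dose. If sirolimus loses proportionately more non-responders than control does, the sirolimus participants who remain look better for a reason unrelated to the drug. If it loses more low responders, they look worse.

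The plan has the information to correct this, because stratum and site are complete. Yet its only named test ignores both. Imputing baseline characteristics does not help here: the chi-square uses no covariates, and the adjusted model uses only factors that are already complete. The ITT label does not tell a reader of the results that randomised participants have been removed.

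**Working it through.** **Inputs from the protocol article.** Sample size {14}: 60 per arm, a 25-point target difference and 10% drop-out, which is 0.10 × 120 = 12 participants. The document gives no figure for this bias and no stratum-specific response or loss rates.

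**Assumptions.** Half of each arm are non-responders. Two sets of true success rates (non-responder / low responder) are tried: 10% / 50% and 20% / 70%. Loss depends only on arm and stratum, so the data are missing at random. Each pattern loses 12 of 120.

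**Formula.** With non-responder share w, success rates p_N and p_L, and loss fractions m_N and m_L, the expected crude proportion in an arm is

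[w(1−m_N)p_N + (1−w)(1−m_L)p_L] / [w(1−m_N) + (1−w)(1−m_L)].

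**Crude comparison when the true difference is zero** (loss given as non-responders / low responders)

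| Rates | Sirolimus loss | Control loss | Sirolimus, crude | Control, crude | Error (points) |
|---|---|---|---|---|---|
| 10/50 | 22.5% / 7.5% | 5% / 5% | (0.03875+0.23125)/0.85 = 31.8% | 30.0% | +1.8 |
| 10/50 | 7.5% / 22.5% | 5% / 5% | (0.04625+0.19375)/0.85 = 28.2% | 30.0% | −1.8 |
| 10/50 | 40% / 0% | none | (0.03+0.25)/0.80 = 35.0% | 30.0% | +5.0 |
| 20/70 | 20% / 0% | 20% / 0% | (0.08+0.35)/0.90 = 47.8% | 47.8% | 0 |
| 20/70 | 20% / 0% | 10% / 10% | 47.8% | 45.0% | +2.8 |
| 20/70 | 20% / 0% | 0% / 20% | 47.8% | (0.10+0.28)/0.90 = 42.2% | +5.6 |

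Simulation agrees (+5.1 for the third row, +1.8 and −1.8 for the first two). At 20/70, moving the non-responder share from 30% to 70% gives +2.2 to +2.8 for the fifth row and +4.7 to +5.6 for the sixth.

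**When the true difference is 25 points in each stratum** (10/50 against 35/75). Under 40% / 0% loss the crude sirolimus proportion is (0.105+0.375)/0.80 = 60.0%, so the difference reads 30.0. Under 7.5% / 22.5% against 5% / 5% it is (0.161875+0.290625)/0.85 = 53.2%, so the difference reads 23.2.

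**Using the strata.** Within a stratum, this kind of loss leaves the expected success rate unchanged. Standardising to the randomised mix gives 0.5 × 10% + 0.5 × 50% = 30.0% in both arms, a difference of 0. In simulation the standardised difference stays within about 0.1 point of the truth in all the 10/50 settings.

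**RR and two-sided rejection at 5% under the null** (simulated; the Mantel-Haenszel RR and Cochran-Mantel-Haenszel test stand in for the planned log-binomial model, and site is not simulated)

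| Rates and pattern | Crude RR | Adjusted RR | Chi-square | Adjusted test |
|---|---|---|---|---|
| 10/50, moderate | 1.06 | 1.00 | 3.7% | 5.0% |
| 10/50, reversed | 0.94 | 1.00 | 3.5% | 4.9% |
| 10/50, 40% / 0% | 1.17 | 1.00 | 6.8% | 5.0% |
| 20/70, sirolimus 20% / 0%, control 10% / 10% | 1.06 | 1.00 | 3.5% | 5.0% |
| 20/70, opposite patterns | 1.14 | 1.00 | 6.2% | 5.0% |

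Without differential loss the chi-square rejects about 3.1% (10/50) or 2.6% (20/70). It is conservative because it ignores the strata.

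**The case against.** The strongest reply is that the plan already contains the remedy. The adjusted RR in {20a} conditions on response stratum and site, and in every pattern above it returns 1.00 under the null. A reader might infer that the plan has no analysis valid under missing at random; the document does not support that. What stands is narrower. The chi-square is the only test named for the primary endpoint, the crude and adjusted RRs are listed side by side, and no rule says which prevails if they disagree. The adjusted model also does not cover loss that depends on other measured factors, such as renal function or titre within stratum.

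A reader might also infer that participants who stop sirolimus will lose their outcome. The document says otherwise. The section on discontinuing the intervention {11b} has those who stop for persistent mild adverse events continue in follow-up. The retention section {18b} asks those who discontinue or withdraw to keep attending visits. Differential loss remains possible, because the trial is open label and only one arm changes drug, but it is not shown to be likely.

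A third tempting reading is that false positives are clearly inflated. Two-sided, the chi-square stays below 5% in the moderate patterns and exceeds it only in extreme ones. The 40% / 0% pattern means 12 of 30 sirolimus non-responders lost and nobody else, which nothing in the document suggests.

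Finally, imputing baseline data is not pointless: {20a} allows a sensitivity analysis adjusting for baseline imbalance. Nor is outcome imputation required. With stratum and site complete, imputing outcomes from those same variables would add little to the adjusted complete-case model.

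**Conclusion.** The point holds in a limited form. The plan states one missing-data assumption and attaches to it a deletion rule and a crude test that need a stronger one. The resulting error is roughly 2 points in a moderate pattern and 5 to 6 points in extreme ones, in either direction, against a 25-point target. It is zero under the null when both arms lose the same mix. These sizes rest on assumed stratum rates, equal strata in the main calculations, and loss of about 10% that depends only on arm and stratum.

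The 10% drop-out allowance covers lost numbers, not bias. The best-worst and worst-best analyses give no protection, because outcomes labelled missing at random never trigger them. The adjusted RR does protect under the stated conditions, so the defect lies in the order of the analyses and the label rather than in a missing method.

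One caution applies to the adjusted RR. The checks above are under the null. A uniform 25-point gain on 10% / 50% means stratum RRs of 35/10 = 3.5 and 75/50 = 1.5, so a single common RR is then only a summary, and its weighting depends on who remains. Standardising to all randomised participants avoids this.

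**What to change.** In {20a}, name the stratum- and site-adjusted analysis as the primary comparison, or a risk difference or RR standardised to the response-stratum and site mix of all randomised participants. Keep the crude chi-square and unadjusted RR as supportive.

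In {20c}:
- State the variables given which outcomes are assumed missing at random.
- Call the analysed set complete-case or modified ITT, and report the exclusions by arm and response stratum.
- Optionally add, as a sensitivity analysis, multiple imputation of outcomes using measured predictors beyond stratum and site.

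The cost is a change of wording and minor extra programming, with no new data collection. The limitation is that any such correction works only for measured predictors of loss.
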